### Plan of statistical analyses

The analyses of primary and secondary outcomes will follow a modified intention-to-treat principle (mITT). All initially randomized patients and GPs and will be included in the analysis according to the group to which they were assigned, minus those who did not fulfil the inclusion criteria after randomization (for example patients with a PPI deprescribing occurring between randomization and intervention).

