### Study population

We will include both patients and their regular GPs if the GP has a regular patient population of more than 100 patients per year. Eligible patients must be affiliated to the French health national insurance system (Caisse Primaire d’Assurance Maladie, CPAM), and have been dispensed more than 300 defined daily doses (DDD) of PPI in the 12 months before baseline, estimated using the local health insurance reimbursement database (SIAM-ERASME). Those patients at risk of gastroduodenal lesions i.e. treated with nonsteroidal anti-inflammatory drugs (NSAIDs) and over 65 years old or treated with either corticosteroids or anticoagulants or platelet aggregation inhibitors will be excluded.

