### Outcome measures

#### Primary outcome

PPI deprescribing will be defined as the proportion of patients achieving a 50% decrease in their PPI reimbursement (Defined Daily Dose (DDD)/year) at the end of the intervention (at 12 months compared to baseline).

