**Fig. 2 Fig2:**
[figure not shown]
First collection from local health insurance database 1 month before baseline and data flow. ^1^PPI DDD/year: Proton pump inhibitors defined daily dose per year; ^2^GPs: General practitioners

Healthcare resource consumption over a one-year period will be collected by combining PPI use and medical expenses related to ambulatory care (histamine-2 receptor antagonists and antacids reimbursements, consultations, technical procedures and laboratory tests). These data will be collected using the local health insurance reimbursement database (SIAM-ERASME) 12 months after baseline.

Hospital service use will be collected using the French National Health Data System (*Système National des Données de Santé*, SNDS) [29].

Measuring health-related quality of life, GERD recurrence and attitudes toward deprescribing, requires sending self-administered questionnaires with pre-paid return envelopes and to scheduling phone calls to minimize missing answers. Thus, the analysis will only be performed on a 10% sample of the population.

Thus, the EQ-5D-5L, GERD Impact Scale and rPATD questionnaires will be mailed to a 10% patient sample in each arm, 1 month before and 12 months after baseline. Patients will return the three self-reported questionnaires to the National Health Insurance by post. Phone calls will be scheduled between 8 and 10 days later to remind patients to return the three questionnaires.

The Health Insurance data managers will pair the data collected from these databases at the patient level, and proceed to data anonymization before transmission to the statistician (Fig. 3).

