**Fig. 3 Fig3:**
[figure not shown]
Second data collection from local health insurance database 12 months after baseline and data flow. ^1^GPs: General practitioners; ^2^SNDS: French national Health data System (*Système National des Données de Santé*)

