### Timeframe

Trial baseline will be planned in mid-November 2020 when deprescribing materials will be mailed to patients and GPs. The three patient reported outcome questionnaires will be mailed 1 month before and 12 months after baseline, mid-October 2020 and mid-November 2021 respectively. Data will be collected 12 months after baseline in mid-November 2021. Study schedule is detailed in the SPIRIT diagram (Table 2).

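### The modified ITT set drops patients whose PPI was deprescribed between randomization and mailing; unless this is judged on pre-mailing records alone, it could remove early responders from the mailed arms

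*Protocol article*

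**What the plan says.** Under Plan of statistical analyses: "The analyses of primary and secondary outcomes will follow a modified intention-to-treat principle (mITT"). Patients stay in their assigned group, "minus those who did not fulfil the inclusion criteria after randomization (for example patients with a PPI deprescribing occurring between randomization and intervention".

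Four other places bear on how that rule would work:

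- **Study population.** Eligible patients must "have been dispensed more than 300 defined daily doses (DDD) of PPI in the 12 months before baseline".
- **Primary outcome.** It is "the proportion of patients achieving a 50% decrease in their PPI reimbursement (Defined Daily Dose (DDD)/year) at the end of the intervention", at 12 months against baseline.
- **Timeframe.** "Trial baseline will be planned in mid-November 2020 when deprescribing materials will be mailed to patients and GPs". Baseline and mailing are thus the same date.
- **Data flow.** The Fig. 2 caption reads "First collection from local health insurance database 1 month before baseline and data flow", and the Fig. 3 caption "Second data collection from local health insurance database 12 months after baseline and data flow". No extraction at the mailing date is described.

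The Limitations section adds that the database shows reimbursements and only estimates intake. The one sensitivity analysis named for the primary outcome, under Missing data, removes patients lost to follow-up. It does not bring the mITT exclusions back.

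**The concern.** The exclusion is made after randomization, on an event of the same kind as the one the trial counts as success. In dispensing data a stop has no date of its own; it shows as a refill that does not come. Someone with tablets in hand who stops just before the mailing, and someone with tablets in hand who stops on receiving it, can leave the same record: a last dispensing before the mailing and none after.

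If the two are confused, the second patient, a true success of the intervention, leaves the analysis. Control practices receive nothing and have no such patients. The brochure goes only to patients in the multi-faceted arm, so the comparison of multi-faceted with single intervention could be affected as well as the comparisons with usual care.

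**Working it through.** The plan gives no figure for this exclusion, so there is none to reproduce. The illustrations below borrow its design figures, which do reproduce. The design effect is 1 + (48.3 − 1) × 0.05 = 3.365. With 33,000/3 = 11,000 patients per arm, the four Table 1 rows for 7% vs 10% give power 0.9938, 0.9903, 0.9299 and 0.9076 (stated 0.994, 0.990, 0.930 and 0.908).

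**1. Length of the gap.** Questionnaires go to a sample in each arm 1 month before baseline. I infer that allocation precedes the mailing by at least about a month.

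**2. Does the inclusion criterion identify the patients in the example?** At 1 DDD a day, stopping 30 days before the mailing leaves 365 − 30 = 335 DDD in the preceding 12 months, still above 300. A patient who loses 30 DDD from the window falls to 300 or below only from 330 or less. Re-checking the criterion therefore finds gap stoppers with about 301 to 330 DDD at extraction and misses those above. The documents do not give the DDD distribution; that this means most of them is a judgement. To remove the rest, a stop must be inferred from refills.

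**3. Two ways to infer a stop.** A small simulation compares them. All its inputs are assumptions: 30-day refills, 0.5% true stops in the gap, later success 10% (intervention) and 7% (control), and immediate response meaning within 14 days of the mailing.

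- Rule A excludes if a refill due before the mailing was missed. Intervention successes removed: 0.
- Rule B excludes if nothing is dispensed on or after the mailing date:

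| Successes responding immediately | Intervention successes removed | Observed intervention | Observed control | Difference |
|---|---|---|---|---|
| 10% | 10% | 9.1% | 6.5% | 2.6 points |
| 25% | 21% | 8.1% | 6.5% | 1.6 points |
| 50% | 40% | 6.3% | 6.5% | −0.2 points |

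The true difference is 3 points. The control rate also falls, because natural stops soon after the mailing date are caught too. The bias comes from the excess in the mailed arm.

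**4. Sensitivity to the share removed.** If a share f of successes is excluded, the observed rate is p(1 − f)/(1 − pf). The worst case is removal in the intervention arm only, with design effect 3.365:

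- 7% vs 10%: f = 10% gives 0.09/0.99 = 9.09%, a difference of 2.09 points and power 0.87. f = 20% gives 0.08/0.98 = 8.16%, 1.16 points and power 0.42. Power at f = 0 is 0.992.
- 7% vs 17%: f = 10% gives 0.153/0.983 = 15.6%, 8.6 points. f = 20% gives 0.136/0.966 = 14.1%, 7.1 points. Power stays above 0.999.
- 7% vs 10% with the same share lost in both arms: 2.75 points (f = 10%) and 2.48 points (f = 20%).

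**5. Cost of excluding nobody.** Take the plan's natural rate of 2 to 7% as a yearly rate, and a one-month gap. 33,000 × 0.02/12 = 55 and 33,000 × 0.07/12 = 193 patients, or 0.17 to 0.58 points, expected equally in every arm. If a common share q has already stopped, the difference is multiplied by (1 − q): 10 points becomes 10 × (1 − 0.0058) = 9.94 at worst.

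**The case against.** The strongest reply is that the text already closes the window at the mailing. The exclusion is tied to the inclusion criteria, the PPI criterion looks back from baseline, and baseline is the mailing date. On that reading no reaction to the mailing can trigger exclusion, and Rule A shows that no bias follows. This stands. A reader might infer that the rule as written removes intervention successes; the documents do not support that.

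Other parts of the reply also stand:

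- A refill missed before the mailing does distinguish an early stopper from a later responder. The records coincide only when the next refill fell due after the mailing.
- The words introducing the example do not make the rule open-ended, since the inclusion criteria bound it.
- That a 50% yearly fall cannot be seen within a month is beside the point, because the exclusion refers to eligibility and not to the outcome definition.
- A reader might put the loss at 1 to 2 points on a 10-point effect. That needs an assumed share of immediate responders, all of them excluded. It would mean 110 to 220 extra exclusions per mailed arm (11,000 × 1 to 2%) against about 18 to 64 natural ones (55/3 to 193/3), an imbalance visible in the participant flow.

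Blinding of data managers and statisticians limits selective use of the rule. It does not stop the mechanism, because an identical query removes more successes wherever the mailing works.

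The SAP may define the query. That does not answer step 2: the protocol's own example reaches beyond its eligibility criterion and calls for a judgement about stopping.

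**Conclusion.** The point holds in a limited form. The protocol fixes a post-randomization exclusion on an outcome-like event, and its example cannot be applied in full by re-checking eligibility. Whether bias follows depends on which records are used: none if they all predate the mailing, and bias toward zero if later dispensing enters. Bias is possible but not shown, and its size cannot be derived from the documents, since the rates of immediate response and the refill pattern are assumptions. Under the plan's larger effects the conclusion of the test would be safe and only the estimate would shrink; with a true 3-point effect the test itself could be lost. This is a cheap improvement to the primary analysis set, and no demonstrated error in the result.

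**What to change.** Define the primary analysis set as all randomized patients who met the criteria at the first extraction, analysed as assigned. Keep the mITT exclusion as a sensitivity analysis with three conditions:

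- It uses only records dated before one common calendar date, the mailing date, which also applies to control practices. Examples are 12-month DDD recomputed at that date and no longer above 300, an excluding co-medication already dispensed, or a refill due before that date and missed.
- The same query runs in all three arms, written while data managers and statisticians are still blinded.
- The number excluded is reported by arm.

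The cost is one paragraph of wording and no new data. The statistical price is the 0.2 to 0.6 points of natural deprescribing per arm from step 5, a dilution of about 0.06 points at most on a 10-point difference.

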#### Primary analysis

PPI deprescribing rate at 12 months will be compared between each arm using a generalized linear mixed model. This model accounts for the random effect of GP practice.

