### Recruitment and allocation

Each GP practice and its associated patients will be defined as an individual cluster to avoid contamination bias between GPs and/or between patients [21]. These clusters will be randomized in three arms using a 1:1:1 ratio. Eligible patients will be identified using the local health insurance reimbursement database.

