### Data collection procedures

Baseline patient variables (age, sex, PPI reimbursement, chronic disease, free complementary health insurance for economically vulnerable patients) and GP variables (age, sex, activity type and city classification) will be collected using the local health insurance reimbursement database (SIAM-ERASME) (Fig. 2).

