### Sample size and power

Preliminary analyses showed that around 33,000 patients, 1300 GPs and 684 practices would meet inclusion criteria in 2017, which corresponds to a mean of 1.9 GPs and 48.3 patients per practice. Using an intraclass correlation coefficient (ICC) of 0.05 thus lead to an inflation factor of 3.365. Literature data suggested a “natural” PPI deprescribing rate between 2 and 7% in the control arm [17, 20, 30].

Assuming an inflation factor of 3.365 and using a two- sided alpha of 0.05, we will have 90% power to detect a minimum true difference of 9.5% of PPI deprescribing rates between the multi-faceted intervention arm and the control arm. These estimates change slightly if different natural deprescribing rates and higher ICCs are assumed (Table 1).

**Table 1 Tab1:** Sample size simulation

“Natural” PPI deprescribing rate	PPI deprescribing rate due to intervention	Patients per cluster	Intracluster Correlation Coefficient	Power
2%	17%	45	0.05	> 0.999
2%	17%	50	0.05	> 0.999
2%	17%	45	0.1	> 0.999
2%	17%	50	0.1	> 0.999
2%	10%	45	0.05	> 0.999
2%	10%	50	0.05	> 0.999
2%	10%	45	0.1	> 0.999
2%	10%	50	0.1	> 0.999
7%	17%	45	0.05	> 0.999
7%	17%	50	0.05	> 0.999
7%	17%	45	0.1	> 0.999
7%	17%	50	0.1	> 0.999
7%	10%	45	0.05	> 0.994
7%	10%	50	0.05	> 0.990
7%	10%	45	0.1	> 0.930
7%	10%	50	0.1	> 0.908

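### The primary mixed model, as described, names no baseline covariates, although prognostic ones are collected; prespecifying adjustment would be a modest, nearly costless gain in precision

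*Protocol article*

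**What the plan says.** Under Primary analysis, the protocol article describes the model in two sentences: "PPI deprescribing rate at 12 months will be compared between each arm using a generalized linear mixed model", and "This model accounts for the random effect of GP practice". It names no fixed-effect covariate and no link function.

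Under Data collection procedures, it lists what the insurance database will supply: "Baseline patient variables (age, sex, PPI reimbursement, chronic disease, free complementary health insurance for economically vulnerable patients"), together with "GP variables (age, sex, activity type and city classification) will be collected using the local health insurance reimbursement database".

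The primary outcome is "the proportion of patients achieving a 50% decrease in their PPI reimbursement" at 12 months, judged against the patient's own baseline. Under Recruitment and allocation, "These clusters will be randomized in three arms using a 1:1:1 ratio"; no stratification is mentioned.

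Patient characteristics appear in two other analyses. The section on characteristics of patients succeeding in deprescribing puts age, sex, socio-economic status, chronic disease and GP into a mixed model for success. The Missing data section imputes the primary outcome from variables associated with it or with its missingness.

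**The concern.** Baseline PPI dose is the value against which the 50% fall is measured, so it may well predict who meets the criterion. The authors also think it worth testing whether age, sex, chronic disease and socio-economic status are associated with success. All of these come from claims, so using them in the arm comparison needs no new data. A main model without them forgoes whatever precision they offer and leaves chance imbalance between randomised practices uncorrected in the estimate.

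A large patient count does not by itself make the matter trivial. In a cluster trial much of the uncertainty in an arm mean comes from differences between practices, and covariates can reduce that part if practice case mix or practice type explains some of it. At stake is the width of the confidence intervals for the three arm contrasts, and the security of having the covariate set fixed before the data are seen.

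**Working it through.** **Inputs from the article (Sample size and power).** "around 33,000 patients, 1300 GPs and 684 practices would meet inclusion criteria in 2017"; 48.3 patients per practice; ICC 0.05, with 0.1 as the alternative in Table 1; two-sided alpha 0.05. Three equal arms give 33,000/3 = 11,000 patients and 684/3 = 228 practices per arm.

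**The article's own figures first.** Design effect = 1 + (48.3 - 1) x 0.05 = 3.365, as stated. Power was recomputed from a two-proportion test with effective size 11,000 / [1 + (m - 1) x ICC] per arm:

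| 7% v 10% | Stated | Recomputed |
|---|---|---|
| m = 45, ICC 0.05 | 0.994 | 0.9938 |
| m = 50, ICC 0.05 | 0.990 | 0.9903 |
| m = 45, ICC 0.1 | 0.930 | 0.9299 |
| m = 50, ICC 0.1 | 0.908 | 0.9076 |

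All other rows exceed 0.999. Table 1 therefore reproduces with no adjustment, and the stated power does not depend on it.

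**Where the variance lies.** The variance of an arm mean is proportional to (1 - ICC)/m + ICC. At ICC 0.05 and m = 48.3 this is 0.95/48.3 + 0.05 = 0.0197 + 0.0500 = 0.0697. The between-practice share is 0.0500/0.0697 = 0.72.

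**Effect of adjustment.** Let Rw2 and Rb2 be the shares of within- and between-practice variance explained. The variance becomes proportional to (1 - Rw2)(1 - ICC)/m + (1 - Rb2) x ICC, so the proportional reduction is 0.28 x Rw2 + 0.72 x Rb2. Neither share is in the article. The ranges below are assumptions: Rw2 from 3% to 10%, Rb2 from 0 to 30%.

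| Assumed Rb2 | Variance reduction | Interval narrower by |
|---|---|---|
| 0 | 1-3% | 0.4-1.4% |
| 10% | 8-10% | 4-5% |
| 20% | 15-17% | 8-9% |
| 30% | 22-24% | 12-13% |

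The last column is 1 - sqrt(1 - reduction). Expressed as practices, 684/(1 - reduction) - 684 runs from about 60 (8.0% reduction) to about 220 (24.35% reduction) when Rb2 is 10-30%. It is about 6 to 20 when Rb2 is 0.

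**On the percentage-point scale.** For 7% v 10% with design effect 3.365, effective size per arm is 11,000/3.365 = 3,269. The 95% half-width of the difference is 1.96 x sqrt[(0.07 x 0.93 + 0.10 x 0.90)/3,269] = 1.35 points. An 8% variance reduction makes it 1.29 points and a 24% reduction 1.17 points.

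**On power.** Dividing the variance by 1/(1 - R2), with R2 now the overall reduction, the least favourable row (7% v 10%, m = 50, ICC 0.1) goes from 0.908 to 0.913 (R2 = 2%), 0.921 (5%), 0.934 (10%) and 0.957 (20%). The same row at ICC 0.05 goes from 0.990 to between 0.991 and 0.998.

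**Chance imbalance.** The 95% range of the standardised difference between two arms is ±1.96 x sqrt(2 x 3.365/11,000) = ±0.05 for a patient-level covariate whose own ICC is 0.05 (an assumption). For a pure practice-level descriptor it is ±1.96 x sqrt(2/228) = ±0.18.

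**The case against.** The strongest reply is that the text does not exclude covariates. It does not call the model unadjusted, and a condensed article commonly leaves the covariate list to a full protocol or analysis plan, which is not shown here. That stands. A reader might infer a deliberate decision to analyse without covariates, but two sentences that are silent on the point cannot support it. The contrast with the predictor analysis, where covariates are named, is suggestive and no more.

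Second, nothing in the comparison is invalid. With about 228 randomised practices per arm the unadjusted estimate is unbiased, and its standard error already allows for chance imbalance. This stands too. A reader might go further and see adjustment as a remedy for the modified intention-to-treat exclusions. The article's example is deprescribing between randomisation and intervention, before any material is mailed, so it shows no arm-related selection for covariates to correct.

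Third, power is ample in every Table 1 scenario, and the gain rests on assumed shares of explained variance. Also true; the between-practice share of 72% says where the variance lies, not that these covariates explain it. It is tempting to answer that the comparison of the multi-faceted with the single intervention is the fragile one. The article gives no smaller expected difference for it: the abstract's Discussion anticipates more than 10% for the multi-faceted arm against both comparators.

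Fourth, adjustment is not entirely without consequence. If the link is logit, covariates change the conditional odds ratio being estimated and do not simply shrink its standard error. GP descriptors are held per GP, with 1.9 GPs per practice, so using them at practice level needs a summarising rule. Both points stand and shape the fix. They do not remove the case for prespecifying patient-level covariates that are already collected.

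**Conclusion.** The point holds as a minor improvement. The primary model as described names no baseline covariates, although plausibly prognostic ones, including the reference value of the outcome, are collected for the trial population. Prespecified adjustment would reduce the variance of the arm comparison by about 1-3% if the covariates explain no between-practice variance, and by about 8-24% if they explain 10-30% of it. This assumes ICC 0.05, 48.3 patients per practice and 3-10% of within-practice variance explained. The formula is for arm means, so it applies to standardised proportions and their differences rather than to a conditional odds ratio.

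The documents do not support calling this an error, a bias or a power shortfall. The unadjusted comparison is valid and its stated power exceeds 90% throughout Table 1. What can be gained is somewhat narrower intervals, some correction of chance imbalance on measured covariates, and a covariate set fixed in advance.

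**What to change.** State in the primary analysis that the mixed model includes, as fixed effects alongside the practice random effect, baseline PPI DDD (continuous), age, sex, chronic disease and free complementary insurance. City classification and activity type are optional, and only with a stated rule for summarising GP descriptors to practice level.

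Report arm-standardised deprescribing proportions and their differences, so that the estimand stays marginal whatever the link. Keep the model without covariates as a sensitivity analysis.

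The cost is a few sentences in the analysis plan and a standardisation step in the programming. No added patients or data are needed. If the full plan already specifies covariates, the article's description needs only a cross-reference to it.
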